### Intervention and control

i.Intervention

The intervention is a prenatal management system (PNMS), which utilizes pictographs and local dialects by (i) using pictographs that reflect local norms and realities to communicate health needs and concerns, (ii) providing ongoing mobile family planning education in local dialects and sending reminder text messages, (iii) communicating emergencies to providers using geographic information system (GIS) and geo-localization, (iv) increasing access to and utilization of antenatal care and skilled delivery, and (v) integrating this technology into selected district health systems.

Upon registration into the PNMS, pregnant women will be provided five e-vouchers; one e-voucher will be automatically redeemed at each prenatal visit, and the account of the health center will be credited. Mobile phones will be provided to eligible pregnant women, along with electronic vouchers that will be redeemed upon antenatal visits and delivery. Each eligible pregnant woman will be assigned five vouchers (four for antenatal visits and one for delivery, including five transportation vouchers). The vouchers will be administered electronically, and the users of the application will communicate their state of health with providers using graphic signs on their phones or direct calls, which on arrival will be sent to the appropriate health personnel. Messages will consist of both audio and text messages. The health personnel will receive this information on their computers as well as on their phones as SMS alerts and will react appropriately.

Training of healthcare providers and community health workers in using the PNMS and training of pregnant women on how to use the features of the mobile application, including the GIS feature during emergencies, will be provided. The proposed interventions (e-vouchers and mobile phone application) are noninvasive and impose no direct adverse effects on the participants. Every woman is assigned a code to her profile that identifies her upon each visit. There are six graphical icons embedded within the app that indicate the following categories: pain, emergency, family planning, antenatal care, medical advice, and postnatal care.

#### Antenatal care package

The focused antenatal care package by the WHO (https://www.who.int/pmnch/media/publications/aonsectionIII_2.pdf) includes essential interventions in antenatal care as listed by the WHO, which include the identification and management of obstetric complications such as preeclampsia, tetanus toxoid immunization, intermittent preventive treatment for malaria during pregnancy (IPTp), and the identification and management of infections including HIV, syphilis, and other sexually transmitted infections (STIs). Pregnancy-related complications, particularly preeclampsia, will be diagnosed and managed. Identification and surveillance of the pregnant woman and her expected child will be conducted. Women and their families will be provided with appropriate information and advice for a healthy pregnancy, safe childbirth, and postnatal recovery, including care of the newborn, promotion of early, exclusive breastfeeding, and assistance with deciding on future pregnancies to improve pregnancy outcomes.

The mobile application consists of both a user interface and web-based platform for providers. The user interface consists of the six icons as described below (see Fig. 3), which pop up on the participants’ mobile phone once the application is downloaded. Upon activating any of the icons at the point of need, the provider will be alerted via the online platform, which is the PNMS. The health care provider can collect patient information (participants) history and demographics, which will help the providers to follow up their patient (participant) based on their history for continuity of care. During antenatal care visits, as participants attend their antenatal care visit, the system will prompt the provider to document the visit and timing and to register the schedule for the next visit, which will auto-generate a reminder message that will be sent to the participant a few days before the next scheduled visit. This is the same protocol that will be used for any additional appointments and during delivery. The features of the mobile application and their specific functions are briefly described below.

**Fig. 3 Fig3:**
[figure not shown]
Graphical presentation of the pre-natal management system

#### Mobile family planning feature

This feature will be audio-recorded in the local language that is understood by everyone in the community, for example, “pidgin English.” In addition, mobile family planning messages will be recorded in their local dialect, and there will be options for listening to the message in multiple dialects. The final mobile family planning message will be developed based on data generated from the formative study.

#### Geographic information system feature

This is the emergency feature. It is also presented graphically on the participants’ mobile phones and activated during emergencies by simply touching the appropriate emergency icon on the screen. The emergency icon signals the provider with the location of the pregnant woman, and the provider or the service driver or an assigned individual can use geo-localization to navigate and reach out to the woman in distress. These individuals will be trained on how to use geo navigation to locate a distressed patient.

The other icons, namely pain and postnatal and medical advice, connect with the providers in the same way; specifically, participants touch the icon, which sends a signal to the provider. The participants can then discuss issues or ask questions as needed. In addition, the pain icon functions in a similar manner to the emergency icon.
ii.Active control group

This group is “business as usual” (standard practice). Women will pay out of pocket for their transportation to antenatal clinics, antenatal care visit services, and delivery. In addition, no mobile phones will be distributed to this group, and, therefore, they will not have access to the mobile family planning and geographic information system (GIS) features. Moreover, those participants who may own mobile phones will be unable to download the application during the pilot study.

### Outcomes

#### Primary outcomes

We used the criteria from Thabane et al. (2010) [50] to conduct feasibility studies to describe our primary and secondary outcomes. The primary outcomes are categorized as feasibility and clinical outcomes, which assess the feasibility of the processes involved and the scientific assessment as follows:

Feasibility outcomes include an assessment of randomization, contamination, enrollment rate, follow up, compliance rate, refusal rate, and adherence rate.

Clinical outcomes (planned for the larger study) include the number of antenatal visits, skilled birth delivery, family planning, and maternal mortality and failure rates.

#### Secondary outcomes

The secondary outcomes include operational and economic outcomes, which assess the resource utilization involved, and management of the software as follows: human resource capacity, equipment availability, district and health area capacities, project timeline, and cost. These outcomes are operationalized in Table 1.

**Table 1 Tab1:** Table indicating feasibility, clinical, operational, and economic outcome variables

Outcome measures	Scale	Type	Measure	Method of analysis
Feasibility outcomes				
Evaluate randomization	Ordinal	Binary	% of health areas with successful stratification and randomization	Feasibility threshold of 95%
Enrolment rate	Nominal	Binary	% of participants with successful enrolment within 6 months into the trial	Feasibility threshold of 50%
Complete follow-up	Ratio	Continuous	% of participants who complete follow-up at 8months into the trial	Feasibility threshold of 80%
Compliance rate	Ratio	Continuous	% of participants who do not follow procedure as allocated	Feasibility threshold of 10%
Contamination	Ratio	Continuous	% of contamination	Feasibility threshold of 10%
Refusal rate	Ratio	Continuous	% of participants who refused to respond	Feasibility threshold of 5%
Adherence rate	Ratio	Continuous	% of participants who adheres to the intervention	Feasibility threshold of 80%
Clinical outcomes				
Failure rate	Ratio	Continuous	% of participants whom intervention (mobile phone features) failed to function according to design	*n* (%)
Mortality	Ratio	Binary	Number of maternal deaths	*n* (%)
Number of ANC visits	Nominal	Binary	Number of ANC visits attended	Mean (SD)
Number of skilled birth delivery	Nominal	Binary	Number of skilled birth delivery	Mean (SD)
Family planning	Nominal	Binary	% using family planning/awareness	*n* (%)
Operational outcomes				
Resource capacity	Nominal	Binary	Average number of human resources	Mean (SD)
Equipment availability	Nominal	Binary	Average number of equipment	*n* (%)
District and health areas capacity	Nominal	Binary	% of resource functionality and communication network	*n* (%)
Project timelines	Nominal	Binary	Average length of follow-up	Mean (SD)
Data collection time	Nominal	continuous	Average time to collect data	Mean (SD)
Matching data from other sources	Nominal	binary	% of success in matching data sources	*n* (%)
Data completeness	Nominal	Binary	% of participants who do not provide complete response	*n* (%)
Acceptability of using mhealth and e-vouchers by participants	Nominal	Binary	% of participants who accept the use mhealth	*N* (%)
Acceptability of using mhealth and e-vouchers by providers	Nominal	Binary	% of providers who accept the use of mhealth	*N* (%)
Use of transportation vouchers	Nominal	Binary	% of women using transportation vouchers	*N* (%)
Economic outcomes				
Total cost of care	Ratio	Continuous	Average total cost of care	Mean (SD)
Cost per woman enrolled	Ratio	Continuous	Average total cost of care per woman enrolled	Mean (SD)
Additional cost due to emergencies	Ratio	Continuous	% with additional emergency cost	*n* (%)

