### Recruitment and follow up

Recruitment into the study will be prospective, and each participant will be followed during their pregnancy until they deliver. Mothers who do not deliver in the hospital will be followed-up in the community by community health workers within 1 week of delivery. The study will run for 18 months to allow time for the outcome to be measured and for enough participants to be enrolled in the study (this includes the formative phase). Recruitment is primarily based on referrals through community health workers, by word of mouth in the community, and through health-educational programs and healthcare workers in respective health clinics. Prior to introducing the intervention, community sensitization and the involvement of village leaders will be carried out in the health areas. Community meetings will be organized to explain the intervention to all community members through a brief pop-up presentation by the project lead and project coordinator. Furthermore, community health workers will be trained to inform all pregnant women about the intervention on an individual basis.

A total of eight community health workers will be involved in the project, two from each health area. Recruitment will occur within 8 months (allowing enough time for all women to deliver within the 18-month study time frame), and each community health worker will be responsible for recruiting approximately 35 pregnant women (approximately five women per month) to attain the estimated sample size. However, these districts have yearly deliveries totaling a minimum of 500 in Bali and over 1000 in the Ndop district [8]. Therefore, the estimated sample sizes are anticipated to be reached within a year. However, considering that all health areas within the district are eligible, the anticipated contingency plan for recruitment will be to recruit individuals from other health areas within the same district or divide the participating district into zones.

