#### Outcome measures

All outcomes will be assessed by self-reports, objective assessments, and face-to-face interviews. The clinical outcomes in Table 1 will be collected objectively by providers directly on the PNMS platform as participants attend their antenatal care visit, and they will also be collected from self-reports by data collectors as follows. All participants in the intervention and control groups will be assessed at the following time points: baseline (T0) at recruitment into the trial, midpoint (T1) at 32 weeks into the trial and endpoint (T2), which is immediately after delivery. For the postnatal period, 2 months immediately after delivery (post-intervention period), data will be collected solely on exclusive breastfeeding, which is at T3 (2 months after delivery). At each time point, participants will be asked the same set of questions plus repeated questions on antenatal care visit, skilled delivery and family planning. Baseline measures will include sociodemographic data on age, gender, income, education, marital status, place of residence, religion, and occupation.

The study timeline is outlined in Table 2, adapted from the Standard Protocol Items: Recommendations for Interventional Trials (SPIRIT) template [51], and data for the tertiary outcomes will be collected at the following time points: T0, T1, T2, T3, as defined above.

**Table 2 Tab2:** Schedule of enrolment, interventions, and assessments in accordance with activities on WHO focused ANC package

TIMEPOINT^a^	June to August 2018	Study period (September 2018 to September 2019)							
	Formative study	Enrolment	Allocation		Post-allocation				Postnatal and Close-out
	Phase I		t0 (Baseline)	(ANC #1 (8–12 weeks)	ANC#2 (24–26 weeks)	t1 (ANC# 3 (32 weeks)	ANC#4	t2 Delivery	t3 Postnatal
Key informant interviews and focus group discussions	X								
Enrolment:									
Eligibility screen		X							
Informed consent		X							
Pre-assessment demographics		X							
Allocation			X						
Interventions									
[Group A e-vouchers and mobile phones]				X	X	X	x	X	X
[Group B control, standard care]				X	X	X	x	X	X
Assessments									
[medical history, examination, drug history, malaria/HIV screening, antenatal history, hep B screening, on ARV, preeclampsia, echography/fetal movements]			X	X	X	x	x	X	
[outcomes, #ANC, delivery, MMR,FP]			X		X		X		X
[Exclusive breastfeeding]									X
CHW weekly follow-up			X	X	X	x	x	X	X
Resource utilization and management	x	X	X	X	x	x	x	x	X

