#### Intervention

During the intervention period from October 2018 to September 2019, the following data will be collected: attendance at ANC1, ANC2, ANC3, and ANC4 visits and the timing of these antenatal visits, followed by a list of variables as outlined in Table 2.

Data will be collected at three different levels. At the hospital and/or health center level, data from the intervention group will be collected directly from the mobile web-based version online PNMS, where the doctor will log in to enroll the patients. The questionnaire will contain characteristics of the baseline data and an antenatal focused package. In the control areas, the data will be collected directly from the District Health Information System (DHIS2) as usual. Data collectors will collect data at different times using Magpi, and these data will be triangulated with the data that are collected by healthcare providers and through community health worker weekly follow-ups. The third level of data collection by community health workers will occur on a weekly basis, and this information will be collected using Magpi, which will allow geo-mapping of participants to help control for loss to follow up through displacement. These data will be triangulated for quality and consistency in both the intervention and control areas.

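### The 80% complete-follow-up criterion is read 8 months into the trial, when recruitment is only ending and, on the plan's own timetable, well under half of the women can have delivered

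*Protocol article*

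**What the plan says.** Follow-up is listed among the feasibility outcomes in the Primary outcomes section. Table 1 (under Secondary outcomes) measures it as the percentage "of participants who complete follow-up at 8months into the trial", judged by "Feasibility threshold of 80" per cent. The enrolment row just above it uses the same phrase: the percentage "of participants with successful enrolment within 6 months into the trial".

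On timing, the Recruitment and follow up section states: "Recruitment will occur within 8 months (allowing enough time for all women to deliver within the 18-month study time frame". The 18 months include the formative phase, and each woman is followed to delivery. The Participants and Eligibility criteria sections admit women at 4 months of pregnancy or earlier. The Outcome measures section puts the endpoint, T2, immediately after delivery. It adds T3 two months later, for breastfeeding data only.

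On the calendar, Table 2 places the formative study in June to August 2018 and then gives "Study period (September 2018 to September 2019", with the postnatal and close-out column inside that period. The Intervention part of the data collection section reads "During the intervention period from October 2018 to September 2019".

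**The concern.** Month 8 of the trial is when the last women enrol, not when follow-up ends. A woman enrolled after about month 3 cannot ordinarily have delivered by then, however well she is retained. The criterion would therefore measure how recently women were enrolled and would say little about retention.

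The Anticipated use of results section says the pilot will inform the larger trial. A primary feasibility threshold that is missed without a single drop-out would misreport retention to whoever makes that decision.

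There is a second, separate difficulty: the article gives two closing dates that do not agree, and the date decides how many late recruits can be observed at all.

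**Working it through.** **Recruitment plan, reproduced first.** The text says "A total of eight community health workers will be involved in the project, two from each health area", each to recruit "approximately 35 pregnant women (approximately five women per month" on average. That is 8 × 35 = 280 women, which equals 2 × 140, the stated size per arm. At 35 per worker, 8 months means 35/8 = 4.4 a month, and five a month means 35/5 = 7 months. The plan is coherent with accrual over 7 to 8 months.

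**Inputs from the article.** Recruitment lasts A = 8 months; entry is at g ≤ 4 months; T2 is at delivery; T3 is 2 months after delivery; the threshold is 80%.

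**Assumptions not in the article.** Accrual is even and starts with the September 2018 study period; drop-out is zero. Term is 9 months, varied to 40 and 37 weeks (4.35 weeks per month). Gestation at entry ranges from all women at exactly 4 months (most favourable) to an even spread from 4 weeks to 4 months.

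**Formula.** A woman enrolled at month r delivers at r + (term − g). With r even over 0 to A, the share delivered by month T is the average of (T − (term − g))/A, held between 0 and 1. For T3, add 2 months.

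**Delivered by month 8, worked cases.**
- 9-month term, all at 4 months: r + 5 ≤ 8, so r ≤ 3, and 3/8 = 37.5%.
- 40-week term, all at 4 months: 5.2 months remain, so r ≤ 2.8, and 2.8/8 = 35%.
- 40-week term, entry spread from 8 weeks to 4 months: 5.20 to 7.36 months remain, mean 6.28, and (8 − 6.28)/8 = 21.5%.

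**Calendar.** June to August 2018 is 3 months and September 2018 to September 2019 is 13, so Table 2 spans 16 months. Eighteen months from June 2018 ends in November 2019, leaving 18 − 3 = 15 trial months. For T3 at month 13 with a 9-month term and entry at 4 months: r + 7 ≤ 13, so 6/8 = 75% fall inside and 25% after close.

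| Entry and term | Delivered by month 8 | Delivered by month 13 | T3 after close at month 13 | T3 after close at month 15 |
|---|---|---|---|---|
| All at 4 months, 9 months | 37.5% | 100% | 25% | 0% |
| All at 4 months, 40 weeks | 35% | 97.5% | 27.5% | 2.5% |
| All at 4 months, 37 weeks | 44% | 100% | 19% | 0% |
| 8 weeks to 4 months, 40 weeks | 22% | 84% | 41% | 16% |
| 4 weeks to 4 months, 40 weeks | 16% | 78% | 47% | 22% |

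**Sensitivity to pace.** With accrual finished in 7 months, the best month-8 share is 40% at a 40-week term and 50% at 37 weeks. To reach 80% by month 8 with a 9-month term and entry at 4 months, 0.80 × 280 = 224 women would have to be enrolled in the first 3 months. Eight workers at five a month enrol 8 × 5 × 3 = 120.

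**The case against.** **The clock may be each woman's own.** The Outcome measures section places T1 32 weeks into the trial, and Table 2 shows t1 as the third antenatal visit, at 32 weeks. The article therefore uses the phrase at least once for a clock that belongs to the participant. Counted from each woman's enrolment, 91% to 100% deliver within 8 months and the threshold is attainable. This stands as a possible reading, so a reader who concludes that the criterion cannot be met on any reading goes too far. But the enrolment row beside it can only be trial time, and nothing in Table 1 marks a change of clock. The 32 weeks also look like gestational age, which is neither trial time nor time since enrolment.

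**The target may be smaller.** The Sample size section also gives 35 per cluster, and four clusters make 140 women. Eight workers at five a month would finish in 140/40 = 3.5 months. The month-8 share would then be 80% if all entered at 4 months with a 40-week term, and nearly 100% at 37 weeks. With spread gestation it would be only 36% to 49%. This reading conflicts with the stated 8 months and with 8 × 35 = 280.

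**T3 is not the reason.** A reader might infer that the criterion fails because T3 visits fall after close-out, or that it fails even on a per-woman clock because T3 comes too late. The documents do not support either. Follow-up is stated to run to delivery, T2 is called the endpoint, and T3 collects breastfeeding data only. Close-out has no bearing on what can be observed at month 8.

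**The enrolment threshold is not a parallel error.** Fifty per cent by month 6 is lenient against the 6/8 = 75% expected under even accrual, but it contradicts nothing. How low to set a pilot's minimum is a design preference.

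**Conclusion.** The criterion is wrong as written on its most natural reading. With 280 women accrued evenly over 8 months and a 9-month term, at most 37.5% can have delivered by month 8 with zero drop-out, against a threshold of 80%. The range is about 16% to 44% over the term and gestation assumptions. The conclusion rests on trial time and on accrual spread over roughly 7 to 8 months, both of which the article supports. If a per-woman clock was meant, delivery is attainable and the fault is that the row does not say so. The article states no rule that missing one threshold stops the larger trial, so the harm is a misleading primary feasibility result and not an automatic decision.

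The closing dates are a separate conflict. On Table 2's September 2019 close, roughly 25% to 47% of T3 visits would fall after close under even 8-month accrual and full-term delivery, or about 19% if every woman delivered at 37 weeks. On the 18-month frame it is 0% to 22%. It cannot be said without qualification that the study closes before many T3 visits: that depends on which date governs.

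**What to change.** Reword the complete-follow-up row of Table 1 as the percentage of all enrolled women with a T2 assessment after their own delivery. Keep the 80% threshold, and evaluate it after the last enrolled woman's T2 assessment is due. Report T3 completion separately.

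Reconcile Table 2's September 2019 close with the 18 months in Recruitment and follow up, and state one closing date together with the last enrolment date it allows. This matters for the reworded criterion too: on the Table 2 date, 78% to 100% of deliveries fall inside the study, so at the lower end a close at month 13 would itself keep the result under 80%.

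The first change costs one reworded table row and a later date for reading the result. The second costs one corrected date. If close-out moves later, it adds some further weeks or months of community health worker contacts of a kind already planned; if enrolment stops earlier, it shortens the 8-month recruitment window. The enrolment row needs no change on this account.
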